**4.7 Study location**

The present project will cover a prospective collection study of patients with elective surgical indication at the Barretos Cancer Hospital, a national reference center for the treatment of cancer patients.

**4.8 Randomização**

Randomization will be generated through the platform - REDCap - creating a random list of entry into the study, separating into group 1 - control (patients who will be transported to the operating room by the traditional method, on a stretcher) and group 2 - experimental (patients who will walk to the operating room), both groups accompanied by their families. In this way, all patients will have an equal chance of being included in both groups.

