**3.2 Secondary objectives**

**3.2.1** To analyze whether the type of transport of the patient classified as PS 0 and 1 has an influence on the degree of depression.

**3.2.2** To analyze whether the type of patient transport classified as PS 0 and 1 has an influence on the degree of patient satisfaction.

**3.2.3**Analyze the patient's anxiety according to the type of transport, according to gender.

**3.2.4** Analyze the patient's anxiety according to the type of transport, according to the socioeconomic level.

1. **METHODOLOGY**

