**4.3 Sample calculation**

Based on the results found by Kojima e*t al.* ([12](#_ENREF_12)) A sample size was calculated to compare proportions. Considering a α error of 0.05 and a power of 1 – β of 0.80, a sample size of 176 patients was reached, with 88 patients allocated to the stretcher group, and 88 patients allocated to the ambulation group.

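### The primary anxiety comparison in 4.9 is unadjusted; adding sex as a covariate is a nearly free gain of about 1 to 5 power points and handles any chance sex imbalance

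*Combined protocol and SAP*

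**What the plan says.** - **Allocation (4.8).** REDCap randomises by "creating a random list of entry into the study, separating into group 1 - control" and a second, experimental group. The only property stated is that "all patients will have an equal chance of being included in both groups". Section 4.6 adds that eligible patients are randomised through REDCap. Block sizes, strata, minimisation and fixed totals per arm are not mentioned.
- **Sample size (4.3).** The method is given as "A sample size was calculated to compare proportions". The stated inputs are alpha 0.05 and power 0.80, and the total of 176 is split evenly: "88 patients allocated to the stretcher group, and 88 patients allocated to the ambulation group".
- **Objectives (3.2).** Objective 3.2.3 is: "Analyze the patient's anxiety according to the type of transport, according to gender". Objective 3.2.4 has the same form: "Analyze the patient's anxiety according to the type of transport, according to the socioeconomic level".
- **Data (4.6).** Gender is among the socio-demographic items in the REDCap instrument, and candidates are identified at admission.
- **Analysis (4.9).** The two transport groups are compared by t-test or Mann-Whitney test for quantitative variables, and by chi-square or Fisher's exact test for categorical ones. No covariate, stratified analysis or interaction term appears, and no method is given for 3.2.3 or 3.2.4.

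**The concern.** The plan asks how anxiety differs by sex but does not use sex in the primary comparison. If sex is related to HADS anxiety, two things follow.

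First, part of the outcome variance that could be removed stays in the error term, so the trial is less precise than its data allow.

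Second, if the single realised allocation leaves more women in one arm, part of the observed difference in anxiety may reflect sex rather than transport, and 4.9 has no planned means of separating the two. Adjusting only after an imbalance has been seen would be a data-driven choice, so the covariate has to be named in advance.

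**Working it through.** **Inputs from the documents.** N = 176, 88 per arm, alpha 0.05, power 0.80 (4.3); equal allocation chance (4.8); unadjusted tests (4.9).

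**Assumptions.** Two-sided alpha; half the patients are women; sex shifts HADS anxiety by g = 0.3, 0.5 or 0.7 SD. The documents give none of these.

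**1. The plan's own figure.** 176 cannot be reproduced, because 4.3 gives neither proportion. It is compatible with, for example, 0.50 vs 0.294 or 0.80 vs 0.608 (two-sided, no continuity correction). I therefore work on the score scale with the standardised effect that gives 80% power at 88 per arm:

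d = (1.960 + 0.842) × √(2/88) = 0.422, with noncentrality 2.802.

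**2. Arm sizes if the list were simple randomisation.** With n₁ ~ Binomial(176, 0.5), P(88/88) = 6.0% and the 95% range for one arm is 75 to 101. Power is 80.0% at 88/88, 79.8% on average and 79.1% at 75/101.

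**3. Sex imbalance under the same model.** The arms differ in share of women by 10 points or more in about 20% of trials, and by 15 points or more in about 4%.

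**4. Error rate of the unadjusted test.** Averaged over randomisations it stays at 5% (simulated 4.97% to 5.02%). Conditional on an imbalance of k = 0.15, with within-sex SD 1, the numerator shifts by δ = g × 0.15 × √44. The t-test's own SD includes the sex variance, so its critical value on this scale is c = 1.96 × √(1 + g²/4). The conditional error is P(|Z + δ| > c).

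| g | δ | c | Error at a 15-point imbalance |
|---|---|---|---|
| 0.3 | 0.298 | 1.982 | 5.7% |
| 0.5 | 0.497 | 2.020 | 7.0% |
| 0.7 | 0.696 | 2.077 | 8.7% |

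**5. Power with sex in the model and sex balanced.** Adjustment removes the sex variance g²/4. If g is in within-sex SDs, the noncentrality becomes 2.802 × √(1 + g²/4). If g is in total SDs, it becomes 2.802 / √(1 − g²/4). Power = Φ(noncentrality − 1.96), against 80.0% unadjusted.

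| g | Within-sex SD | Total SD |
|---|---|---|
| 0.3 | Φ(2.833 − 1.96) = 80.9% | Φ(2.834 − 1.96) = 80.9% |
| 0.5 | Φ(2.888 − 1.96) = 82.3% | Φ(2.893 − 1.96) = 82.5% |
| 0.7 | Φ(2.968 − 1.96) = 84.3% | Φ(2.991 − 1.96) = 84.9% |

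**6. Which change earns the gain.** Simulation with 60,000 trials per cell, total SD 1, half women, effect 0.4225 SD:

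| Allocation and analysis | g = 0.3 | g = 0.5 | g = 0.7 |
|---|---|---|---|
| Simple, unadjusted | 79.4% | 79.3% | 79.5% |
| Simple, sex in model | 80.1% | 81.6% | 84.0% |
| Stratified, sex in model | 80.6% | 82.2% | 84.4% |

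Adjustment adds 0.7, 2.3 and 4.5 points. Stratified allocation then adds 0.5, 0.6 and 0.4. An analytic check agrees: simple allocation inflates the variance of the adjusted estimate by about 1.2% on average, which is about 0.4 points of power.

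**7. Within-sex comparisons (3.2.3).** For the same effect in a stratum of 88, power is 51% if balanced and 49% at the edge of the 95% range. In a stratum of 53 (30% of 176) it is 34% and 31%. Stratum size, not imbalance, is the limit.

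**The case against.** The strongest objection is that nothing in the plan is invalid. Randomisation makes the unadjusted test correct on average, the documents do not say that sex is strongly prognostic, and 3.2.4 gives socioeconomic level the same standing as sex. All of this stands. The gain depends on an assumed sex effect, and at 0.3 SD it is about one point. Adjustment is still worth planning because the downside is so small: with no sex effect the model gives up one residual degree of freedom (173 instead of 174). Sex is a simple two-level covariate fixed before allocation. Socioeconomic level could be added in the same way if its categories are defined in advance.

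A reader might infer three stronger things, none of which the documents support.

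- *That 4.8 prescribes an unrestricted list.* It is silent on restriction. A pre-generated list could be blocked or could hold 88 of each arm, so this is missing detail.
- *That unequal arms cost material precision.* On average the cost is about 0.2 power points.
- *That sex imbalance biases the comparison.* The inflated error rates in step 4 apply only given a 15-point imbalance, and imbalances that large arise in about 4% of trials.

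Stratifying the list would also not secure 88 analysed per arm. Under 4.6 and section 5, consent is sought after transport and the questionnaires, and patients who do not sign leave the study after allocation.

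**Conclusion.** The point holds as a low-cost improvement to the primary analysis in 4.9. Prespecifying sex as a covariate takes power from 80% to about 81%, 82% or 84-85% for sex effects of 0.3, 0.5 or 0.7 SD, and it removes the conditional distortion of about 6% to 9% that the planned t-test would carry at a 15-point sex imbalance. These figures assume half women, a two-sided test, a roughly normal score and a true effect of 0.422 SD; none of these assumptions is in the documents. They apply to the score scale and do not carry over directly to a dichotomised outcome.

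The lack of blocking or stratification in 4.8 is a reporting gap of little consequence. Adjustment does not cure the low power of the sex-specific comparisons in 3.2.3.

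**What to change.** - **In 4.9.** Make the primary anxiety comparison a linear model of the HADS anxiety score on transport group with sex as a covariate, and report the adjusted mean difference with its 95% confidence interval. If the primary outcome is to be dichotomised, as the sample-size method in 4.3 suggests, use logistic regression on group and sex. Keep the unadjusted test as a supporting analysis. Fix this before outcomes are compared by arm.
- **In 4.8.** State the type of list actually used and any block sizes or strata. Stratifying by sex with randomly varying, concealed blocks is optional. It makes allocation slightly more predictable in an open trial. It may also mean a mid-trial change of table, since the document is dated 2020 and the schedule in section 7 starts data collection in 2019.
- **Cost.** About two sentences of text and one degree of freedom. The change needs no extra patients, visits or data items.

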**4.9 Statistical analysis**

Initially, the data of our sample will be described through measures of central tendency (mean and median) and dispersion (standard deviation and quartiles) for all quantitative variables. For the qualitative variables, we will use tables containing the absolute and relative values of each category of variables. Subsequently, in order to observe the difference between the study groups (Stretcher x Walking) in relation to emotional repercussion, degree of satisfaction and anxiety, we will use statistical tests considering the significance of 0.05. If the variables to be listed have a Normal distribution, we will use the T-test, and if not, we will apply the Mann-Whitney test. For categorical variables, we will use the Chi-square or Fischer's exact tests, depending on the characteristics of the data. For such analyses, we will use the SPSS version 21 software, and the help of the Center for Epidemiology and Biostatistics (NEB) of the Barretos Cancer Hospital.

**5. ETHICAL ISSUES**

This project is ethically and methodologically in accordance with the Guidelines and Regulatory Standards for Research involving Human Beings (Resolution 466/12 of the National Health Council) and will be submitted to the Institutional Review Board (IRB) of the Barretos Cancer Hospital. Patients will sign an informed consent form to participate in the study (APPENDIX 3). Failure to sign the term will result in the patient's non-participation in the study, but will not interfere with the patient's treatment at the institution.

**5.1 Risks to the Participant**

There is a risk of breach of data confidentiality between the members of the study, but this will be avoided as much as possible, as well as the minimum risk of falls, since a specific group will be taken to the operating room walking. And to minimize these risks, we will use the fall risk scale used in the hospital's routine, not exposing any patient to complications. The patient will be accompanied by the stretcher bearer and his family member to the operating room, for possible support if he feels unwell during this journey.

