**4.2 Sample**

To select these patients, we will use the fall risk assessment scale adopted in the hospital routine for patients over 60 years of age, together with the *Eastern Cooperative Oncology Group (ECOG PS)*scale (Table 1), with only patients being classified as no risk or with minimal risk,*,* according to the fall risk scale (Table 2), and patients with SP 0 and 1.

**Table 1 -ECOG Performance Status** (Grupo de Oncologia*Eastern Cooperative, [name].)*

| Degree | **ECOG PERFORMANCE STATUS** |
| --- | --- |
| 0 | Fully active, able to develop all your performance, without any restrictions. |
| 1 | Restrictions on strenuous activities, while maintaining normality in their daily practice. |
| 2 | He still retains his capacity for self-care, but he is unable to perform any work activity, and if he does, it is in less than 50% of waking hours. |
| 3 | Limited capacity for self-care; confined to a bed or chair for 50% of waking time. |
| 4 | Completely disabled, unable to exercise self-care, totally confined to a bed or chair. |
| 5 | Death |

**Table 2: -**SCALE FOR ASSESSING THE RISK OF FALLING (Adapted from Jonhs Hopkins 2007)

| Zero = No Risk 1-5 = Low Risk 6-13 = Moderate Risk > 13 = High Risk | |
| --- | --- |
| **Risk Factor** | **Punctuation** |
| 1. **Age**(select option 1) |  |
| •         60 – 69 years old | 1 |
| •         70 – 79 years old | 2 |
| •         Greater than or equal to 80 years old | 3 |
| 2. **Fall history** |  |
| •         Drop in the last 6 months before admission | 5 |
| 3. **Eliminations**(select option 1): |  |
| •         Incontinence | 2 |
| •         Urgency or change in frequency | 2 |
| •         Urgency/change in frequency and incontinence | 4 |
| 4. **Medications** |  |
| •         Use of 1 of the options | 3 |
| •         Use of 2 or more options | 5 |
| •         Underwent sedative procedures within the last 24 hours | 7 |
| 5. **Use of Equipment:**any equipment used by the patient, such as catheters, venipuncture, among others (select 1 option) |  |
| •         Presence of 1 device | 1 |
| •         Presence of 2 pieces of equipment | 2 |
| •         Presence of 3 or more devices | 3 |
| 6. **Mobility**(multiple selection allowed) |  |
| •         Needs assistance or supervision for movement, transfer or ambulation | 2 |
| •         Unstable gear | 2 |
| •         Visual and/or hearing impairment that affects movement | 2 |
| 7. **Cognitive**(multiple selection allowed): |  |

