**4.5 Non-eligibility criteria**

- Patients who, moments before surgery, present an adverse event that may jeopardize walking to the operating room.
- Patients who have a physical disability and need help to walk.
- Patients who have an indication for a bed in the Intensive Care Unit (ICU)
- Patients who have previously diagnosed psychiatric disorders (severe depression, anxiety disorder, panic, among others).
- ECOG patients > 1.
- Patients who do not have a companion on the day of surgery.
- Patients using anxiolytic and antidepressant medications.

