**4.6 Data Collection**

A research instrument will be made on the REDCap data platform. In it, we will collect socio-demographic data such as: date of admission, date of birth, weight, height, gender, ethnic group, current residence, contact telephone number, name of the companion and their degree of kinship, socioeconomic level, education. We will use the source document (medical record) for information such as: classification of malignant tumors (TNM), classification of performance status according to comorbidities, classification of the fall risk scale, which is performed at the time of the patient's hospitalization by the employee responsible for the same, medications in use, other surgeries, complementary exams confirming the presence of cancer, the type and location of the neoplasm, date of surgery, surgical size.

Patients will be identified as potential participants for the study at the time of their admission. Fulfilling all the eligibility criteria, it will be randomized randomly through the REDCap platform, and the orientation of which group the patient fell will be carried out, for the nursing professional (stretcher bearer) who will take him to the operating room.

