**5.2 Benefit to the participant**

We considered finding a relationship between the way these patients were taken to the operating room and the degree of anxiety presented by the patient before the surgical procedure. It can change the routine of transporting patients to the operating room, since they are patients in good physical condition, and may add some psychological benefit, removing the idea of illness and incapacitation in the face of this simple journey.

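### Falls are the named risk of walking to theatre, but the plan nowhere provides for recording falls, near-falls, unwell episodes or unfinished walks, so a change of routine could be supported without a count of that harm

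*Combined protocol and SAP*

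**What the plan says.** Section 5.1 names two risks: loss of confidentiality and "as well as the minimum risk of falls, since a specific group will be taken to the operating room walking". It offers two safeguards. One is screening: "we will use the fall risk scale used in the hospital's routine, not exposing any patient to complications". The other is the escort of stretcher bearer and relative, "for possible support if he feels unwell during this journey". So the protocol foresees both a fall and a patient who becomes unwell on the way.

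Section 4.6 describes the data. Sociodemographic fields go into REDCap, and for the clinical fields the text reads "We will use the source document (medical record) for information such as", followed by examples. The one fall-related example is the "classification of the fall risk scale, which is performed at the time of" hospital admission, that is, before transport. The fall-history item of the scale (section 4.2, Table 2) is "Drop in the last 6 months before admission", which also predates the journey. Section 4.6 then adds the HADS and Sati-Cir questionnaires, given on arrival in the operating room. Appendix 2, Part A asks how the patient was taken and offers two answers, stretcher bearer or walking.

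The objectives (sections 3.1 and 3.2) and the analysis (section 4.9) cover anxiety, depression, satisfaction and emotional impact. Neither contains a safety objective, variable or table. Section 5.2 gives the intended use of an association between transport and anxiety: "It can change the routine of transporting patients to the operating room". Section 2 says much the same about daily practice.

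**The concern.** The trial compares the hospital's standard way of taking patients to theatre with an alternative whose specific physical risk the protocol itself identifies. If the result favours walking, the practical question is whether the gain in anxiety or satisfaction comes without an unacceptable number of falls or failed journeys. The plan as written could answer the first half and would be silent on the second.

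This is more than a missing detail of reporting. A near-fall or a brief unwell episode in a corridor may leave no trace in the medical record, so what is not noted at the time may not be recoverable at analysis.

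**Working it through.** **1. Is a transport event planned for anywhere?** Setting the relevant sections side by side:

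| Place | What it holds | Fall or unwell episode on the way? | Walk stopped or mode changed? |
|---|---|---|---|
| 3.1, 3.2 Objectives | Anxiety, depression, satisfaction, two anxiety subgroup questions | No | No |
| 4.2 Table 2, 4.6 | Fall-risk class at admission, fall history before admission | No, predates transport | No |
| 4.6 Questionnaires | HADS, Sati-Cir | No | See next row |
| Appendix 2, Part A | Self-report: stretcher bearer or walking | No | In part: a complete switch would show against the allocation. No reason is asked, a mixed journey has no answer option, and a non-respondent leaves no answer |
| 4.9 Analysis | Group comparisons of emotional outcomes and satisfaction | No | No |
| 5.1 Risks | Screening and escort | Foreseen, no recording stated | No |

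**2. Does screening make counting unnecessary?** In Table 2 a fall in the previous 6 months scores 5, and low risk runs from 1 to 5. A patient under 60 with a recent fall and no other points scores 5 and is admitted by section 4.4. Screening lowers the risk but does not remove it.

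**3. The plan's own figure.** Section 4.3 gives 176 patients, 88 per arm, for a comparison of proportions at alpha 0.05 and power 0.80. It cannot be reproduced because the two proportions are not stated. Several pairs fit 88 per arm: for example 0.50 against 0.294, or 0.80 against 0.608, two-sided without continuity correction. Nothing below depends on it beyond n = 88 walkers.

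**4. What recording would give if no event occurred.** The exact upper limit for 0 events in n is 1 − a^(1/n).

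- One-sided 95%: 1 − 0.05^(1/88) = 0.0335, reported as 3.3% (unrounded 0.03347).
- Upper limit of the two-sided 95% interval: 1 − 0.025^(1/88) = 0.0411, or 4.1%.
- Rule-of-three check: 3/88 = 0.0341, or 3.4%.

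**5. Chance of seeing at least one fall among 88 walkers.** The formula is 1 − (1 − p)^88. The documents give no fall rate, so p is an assumption shown over a range.

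| Assumed true rate p | Expected falls, 88p | Chance of at least one |
|---|---|---|
| 0.1% | 0.09 | 1 − 0.999^88 = 8% |
| 0.5% | 0.44 | 1 − 0.995^88 = 36% |
| 1% | 0.88 | 1 − 0.99^88 = 59% |
| 2% | 1.76 | 1 − 0.98^88 = 83% |

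**6. Could the arms be compared formally?** Not usefully. With 88 per arm, 0.1% against 5% would be detected with about 54% power (two-sided 0.05, normal approximation, which is rough for such sparse counts). The record would be descriptive.

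**The case against.** The strongest case on the other side is that events should be few and the plan already handles the risk. Patients are 18 to 70, ECOG 0 or 1, at zero or low fall risk, able to walk without help, and escorted. If the true rate is 0.1% or 0.5%, no fall at all is the likelier outcome, and the upper limit would still be 3.3% to 4.1%. The table could not establish safety, and the plan says only that practice can change. This stands, and it limits the value of the data. It does not justify having no count: zero recorded events with a stated limit is information, whereas no record supports no statement. Unwell episodes and stopped walks may also be more frequent than falls, although the documents give no rate for them.

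A second objection is that the lists in section 4.6 are introduced as examples and the REDCap form is not reproduced, so an unlisted field may exist. This also stands. The supportable statement is that no collection is planned in the text.

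Four stronger readings are tempting and should be resisted.

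- A reader might infer that a change of transport mode leaves no trace. The Sati-Cir item captures it in part.
- A reader might infer that section 4.5 removes walkers who fall, since it excludes "Patients who, moments before surgery, present an adverse event that may jeopardize walking to the operating room". Its natural meaning is an event before the walk. It does not mention patients who fall or stop during it.
- A reader might infer that the walking arm would look safer and calmer than it was. No safety result is planned, so it cannot look safer in any table. Consent follows transport and the questionnaires, and those who do not sign do not take part (sections 4.6 and 5), so selective loss is possible, but nothing shows that it will occur. The effect of an isolated loss would be small: if one missing walker scored 10 HADS anxiety points above the rest (an assumption), the arm mean would move by 10/88 = 0.11 points on a 0 to 21 scale.
- A reader might infer that any conclusion on routine should depend on the safety table. No criterion is available, and 88 walkers could not supply a meaningful one.

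**Conclusion.** The concern holds in this form: the protocol names falls as the risk of the walking arm and foresees patients becoming unwell on the way, but plans no record or report of these events. A change of transport routine could therefore be supported with no count of the named harm.

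In size, this is the difference between no safety statement and a modest one: an upper limit of 3.3% (one-sided) or 4.1% (two-sided) if all 88 walkers are recorded and none falls. Incomplete recording would widen these limits. The chances of observing a fall rest on assumed rates. The conclusion also assumes that the undisplayed REDCap form holds no unlisted transport field. The change should be made because it is cheap and the information may not be recoverable later. It does not call the comparison of anxiety into question.

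**What to change.** **Section 4.6.** Add a brief REDCap transport record for randomised patients in both arms, as far as the post-transport consent rule (sections 4.6 and 5) and the ethics committee allow. Fields: transport actually used; journey completed or converted, with the reason; fall; near-fall; felt unwell. The accompanying stretcher bearer reports these on arrival. The staff who already administer the questionnaires enter them, since the plan gives the stretcher bearer no data-entry role. The record should not depend on the patient having answered Sati-Cir. It adds data items only and sets no rule for patient care.

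**Section 4.9.** Add one descriptive table: counts by randomised arm with exact 95% intervals, and the number randomised for whom no data are available.

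**Reporting.** Beside any conclusion on changing routine, state that the safety data are descriptive only and give the interval, for example the 3.3% or 4.1% upper limit if no event is seen in 88 walkers.

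**Cost.** A few REDCap fields, one table, a little more data entry and no extra staff. The ethics committee would need to agree what may be kept for patients who do not sign. The interval will be wide.
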